## Abstract

**Introduction:**

Current practices for renal replacement therapy in intensive care units (ICUs) remain poorly defined. The DOse REsponse Multicentre International collaborative initiative (DO-RE-MI) will address the issue of how the different modes of renal replacement therapy are currently chosen and performed. Here, we describe the study protocol, which was approved by the Scientific and Steering Committees.

**Methods:**

DO-RE-MI is an observational, multicentre study conducted in ICUs. The primary end-point will be the delivered dose of dialysis, which will be compared with ICU mortality, 28-day mortality, hospital mortality, ICU length of stay and number of days of mechanical ventilation. The secondary end-point will be the haemodynamic response to renal replacement therapy, expressed as percentage reduction in noradrenaline (norepinephrine) requirement. Based on the the sample analysis calculation, at least 162 patients must be recruited. Anonymized patient data will be entered online in electronic case report forms and uploaded to an internet website. Each participating centre will have 2 months to become acquainted with the electronic case report forms. After this period official recruitment will begin. Patient data belong to the respective centre, which may use the database for its own needs. However, all centres have agreed to participate in a joint effort to achieve the sample size needed for statistical analysis.

**Conclusion:**

The study will hopefully help to collect useful information on the current practice of renal replacement therapy in ICUs. It will also provide a centre-based collection of data that will be useful for monitoring all aspects of extracorporeal support, such as incidence, frequency, and duration.

## Introduction

The systemic inflammatory response syndrome is characterized by widespread endothelial damage caused by persistent inflammation from both infectious and noninfectious stimuli. The host employs hormonal and immunological mechanisms to counter the systemic inflammatory response syndrome. Hypoperfusion and shock result when homeostatic mechanisms are no longer able to keep the system in balance, leading to organ dysfunction [1].

Septic shock can be defined as sepsis with hypotension, despite adequate fluid resuscitation, along with evidence of perfusion abnormalities. It is the leading cause of acute renal failure (ARF) and mortality in intensive care patients. The pathogenesis usually involves a nidus of infection, which progresses to a bloodstream infection, followed by activation of mediators and eventual shock or multiorgan failure [2]. Both septic shock and severe bacterial infections are associated with increased levels of plasma cytokines such as tumour necrosis factor-α, IL-1, IL-6, IL-8 and IL-10, IL-1 receptor antagonist, and soluble tumour necrosis factor receptors types I and II. These mediators are produced in response to constituents of both Gram-negative and Gram-positive bacteria. Lipopolysaccharides of Gram-negative bacteria, and peptidoglycans, lipoteichoic acid and exotoxins of Gram-positive bacteria are largely responsible for the initial inflammatory cascade[3,4].

Various continuous and intermittent modalities of renal replacement therapy (RRT) are currently used. There has been slow acceptance of continuous RRT (CRRT) in intensive care units (ICUs) for the management of ARF, but this therapy is not new. In 1977 Kramer and coworkers [5] developed this technique following their accidental accessing of the femoral artery rather than the vein, creating an arterovenous circuit that yielded a very primitive but innovative approach. Problems with low blood flow and coagulation meant that this idea remained dormant for some time. It was not until the application of blood pumps and the substitution of arteriovenous with venovenous circuitry that the current practice of CRRT was born. In recent years remarkable advances in CRRT technology have been made, driven by nephrologists dedicated to improving efficiency and function. Today, however, intensivists are the most familiar with these techniques. Nevertheless, in some countries such as the USA, CRRT is still infrequently employed [6]. Other modalities include intermittent haemodialysis (IHD), slow extended daily dialysis [7], or daily haemodialysis [8]. Some of the reasons for the considerable variability worldwide in extracorporeal treatment of ARF include local practice (e.g. whether management is by nephrologists or intensivists), the centre's experience with the various techniques, organization and health resources. Various methods of extracorporeal treatment, whether intermittent or continuous, are currently being employed and no guidelines exist. This variability was highlighted in a recently completed observational study (the Beginning and Ending of Supportive Therapy for the Kidney [BEST Kidney] trial), which collected data on ARF management in 1743 patients in 54 ICU from 23 countries worldwide.

The practice of CRRT has apparently not changed, even following the prospective studies conducted by Ronco and coworkers [9]. Despite the positive findings of that prospective trial, the practice of a higher intensity CRRT has not been widely adopted into routine ICU practice. The most outstanding examples are Australia and New Zealand, where almost 100% of treatments are CRRT. A survey of several units active in the Australian and New Zealand Intensive Care Society Clinical Trials Group ([name], unpublished data, 2002) found that very few units had adopted the intensive CRRT regimen proposed by Ronco and coworkers [9]. Data from such Australian units shows instead that the vast majority (>90%) prescribe a 'fixed' standard CRRT dose of 2 l/hour, which is not adjusted for body weight. Thus, a 100 kg man would receive 20 ml/kg per hour – the dose shown to have the worst outcome in the study by Ronco and coworkers [9]. In another recent study that involved several Australian units (the BEST Kidney study), the median body weight for Australian patients was 80 kg, thus indicating that the vast majority receive a CRRT intensity of approximately 25 ml/kg per hour of effluent. Finally, although in the study conducted by Ronco and colleagues [9] the technique of CRRT was uniform in the form of continuous venovenous haemofiltration (CVVH) with postfilter fluid replacement, current practice includes a variety of techniques in addition to CVVH, such as continuous venovenous haemodialysis (CVVHD) and continuous venovenous haemodiafiltration (CVVHDF). Scarce information exists on the practice of CRRT in Europe, particularly regarding the actually delivered dose of therapy in critically ill patients with ARF (i.e. in those who could potentially derive more benefit from high volume convective therapy).

In a recent preliminary collaborative study [10] we reported that there was no significant difference between prescribed and delivered ultrafiltration rate (both in ml/min and in l/hour), which was related to the reduced down-time associated with the technique. However, of greater relevance is that the dose of dialysis was over 40 ml/kg per hour.

If we are to understand how dialysis doses are actually delivered in routine clinical practice in ICUs, an observational clinical study is needed to confirm how, to what extent and with what clinical indication the different modalities of RRT are administered. With this in mind we have initiated the DOse REsponse Multicentre International collaborative initiative (DO-RE-MI) trial. The primary end-point of DO-RE-MI is mortality (ICU mortality, 28-day mortality and hospital mortality), and the secondary end-point is the haemodynamic response to RRT, expressed as percentage reduction in noradrenaline (norepinephrine) requirement to maintain blood pressure.

## Materials and methods

Figure 1 presents a study flowchart. Only incident patients with an indication for RRT will be recruited. The study is intended to describe current practices of RRT in all patients admitted to ICUs who are in need of RRT, with or without ARF. All data listed herein will be entered in electronic case report forms (CRFs) that are available via the internet [11]. The following rules will be applied without exception:

First, all patient data will be entered anonymously. To this aim, each centre will have a code, and patients will be consecutively assigned a unique number. Under no circumstances will there be any written or oral transmission of data that may make it possible to identify any patient. Failure to adhere to this will be followed by cancellation of the data from the website by the webmaster.

Second, data for each patient will be entered in a separate CRF. These data may be copied from paper CRFs in order to make the reporting of data from bed to computer station easier. All fields may be amended at any time until the patient's CRF is completed and closed. At this point, one may access the patients' CRF but it will be no longer be possible to amend the CRF. In the case of overt inconsistency, corrections must be detailed in writing (e-mail) by the person responsible for data quality for the centre or by the center itself. In all cases, no corrections will be permitted in the absence of an express written request. The person responsible for data quality will have access to the centre's CRF in printed form only. A registry will collect correspondence between the person responsible for data quality and the centre.

Third, completion of some fields in the CRF is mandatory. Failure to complete them will prevent progression to the following CRF and closure of the opened CRF. Failure to complete a CRF electronically will result in the patient being excluded from the study.

Finally, Each centre will be able to open CRFs for its own patients but never CRFs for patients from other centres.

### Case report form compilation

A guide to CRF compilation is presented in Table 1.

#### Case report form: Admission (step 1)

This CRF will automatically provide the patient's consecutive number. The user must enter the following data:

• sex,

• date of birth,

• weight,

• height,

• date/time of hospital admission,

• premorbid plasma creatinine levels,

• date/time of ICU admission,

• diagnosis at admission,

• Simplified Acute Physiology Score (SAPS) II (the index will be automatically calculated once each requested field is completed),

• Sequential Organ Failure Assessment (SOFA; the index will be automatically calculated once each requested field is completed).

#### Case report form: Criteria to initiate RRT (step 2)

This CRF will automatically provide the patient's consecutive number. The user must enter the date and time when the following clinical events (indexed numerically) occurred:

• 1. Oliguria (urine output <200 ml/12 hours),

• 2. Anuria (urine output <50 ml/12 hours),

• 3. High urea/creatinine,

• 4. Hyperkalaemia (>6.5 mmol/l or rapidly rising potassium),

• 5. Metabolic acidosis,

• 6. Fluid overload,

• 7. Hyperthermia (>41°C),

• 8. Immunomodulation,

• 9. What RIFLE (Risk Injury Failure Loss of function End stage renal disease) criteria [12] are applicable?

• 10. Others (to specify)

The user will also be asked to prioritize the criteria (from 1 to 3) when two or more specified. In addition, the modality chosen must be specified (defined as following and indexed numerically)

• 1. CVVH (as defined as ≤ 35 ml/kg per hour ultrafiltration rate in postdilution or <40 ml/kg per hour in predilution),

• 2. CVVHDF (defined as use of dialysate + replacement [define]),

• 3. High volume haemofiltration (defined as >35 ml/kg per hour in postdilution or >45 ml/kg per hour in predilution),

• 4. Pulse high volume haemofiltration (from 85 ml/kg per hour to 100 ml/kg per hour for 6–8 hours, followed by CVVH at 35 ml/kg per hour),

• 5. Coupled plasma filtration adsorption (CPFA) plus CVVH ,

• 6. IHD ('intermittent' includes conventional haemodialysis and slow extended daily dialysis, thereby encompassing all treatments in which sessions are separated from one another for 10 hours or more).

The CRF will then permit the user to specify any other relevent criteria, including the following:

• Staff problems,

• Technical problems,

• Product (e.g. fluids, lines, filters, machine) availability problems,

• Logistics,

• Others (to be specified).

#### Case report form: Modality-specific assessment time (step 3)

On the basis of the modality chosen in the 'Criteria to initiate RRT' CRF (see above), a specific CRF will be opened. The CRF for IHD will require data entry at baseline, at 4 hours and at treatment end. The CRF will automatically indicate the different visits (i.e. 0.0, 4.0, and treatment end). The CRF for **IHD **will request the following information:

• Decision taken (date/time),

• Start (date/time),

• Prescribed duration (only at assessment time 0),

• Delivered duration,

• Prescribed blood flow rate (only at assessment time 0),

• Delivered blood flow rate,

• Total weight loss (kg/session),

• Type of haemodialyzer (specify only commercial name),

• Surface of haemodialyzer (m^2^),

• Type of buffer (code number for lactate or bicarbonate),

• Anticoagulation (code number for heparin, citrate, prostacyclin, saline flushes, no anticoagulation),

• Arterial site of vascular access (code number for radial, femoral, pedidial, axillary access),

• Venous site of vascular access (code number for subclavian catheter, femoral catheter, jiugular, axillary catheter),

• Type of vascular access (code number for double lumen catheter, single lumen catheter),

• Vascular access gauge,

• Treatment interrupted (date/time),

• Resumption of treatment (specify date/time),

• End (day/time),

• Change in modality.

The CRF for **CVVH **will require data entry at 0 hours, at 1 hour, 3 hours, 6 hours, 12 hours, 24 hours, and every 24 hours thereafter and at treatment end. The CRF will automatically indicate the different assessment times (i.e. 0.0, 1.0, 3.0, 6.0, 12.0, 24.0, and so forth). Assessment times at 1.0, 3.0, 6.0 and 12.0 are optional, while assessment time at 24.0 and for multiples of 24 are mandatory. The following information will be requested:

• Decision taken (date/time),

• Start (date/time),

• Prescribed duration (only in assessment time 0),

• Delivered duration,

• Prescribed blood flow rate (only in assessment time 0),

• Delivered blood flow rate,

• Prescribed effluent (ml/hour; only at assessment time 0),

• Total effluent (ml/24 hours; only at assessment time 24 or last assessment time before treatment interruption/end),

• Prescribed reposition rate (ml/hours; only at assessment time 0),

• Total reposition (ml/24 hours; only at assessment time 24 or last assessment time before treatment interruption/end),

• Total volume removed from the patient (ml/24 hours),

• Type of haemodialyzer (as above),

• Surface (m^2^),

• Type of buffer,

• Anticoagulation (as above),

• Arterial site of vascular access (as above),

• Venous site of vascular access (as above),

• Type of vascular access (as above),

• Vascular access gauge,

• Treatment interrupted (date/time),

• Resumption of treatment (specify date/time),

• End (day/time),

• Change in modality.

The CRF for **CVVHD **(Note: I would suggest to indicate the modality in bold for clarity's sake) will require data entry at 0 hours, at 1 hour, 3 hours, 6 hours, 12 hours, 24 hours, and every 24 hours thereafter and at treatment end. The CRF will automatically indicate the different assessment times (i.e. 0.0, 1.0, 3.0, 6.0, 12.0, 24.0, and so forth). Assessment times at 1.0, 3.0, 6.0 and 12.0 are optional, while assessment times at 24.0 and for multiples of 24 are mandatory. The following information will be requested:

• Decision taken (date/time),

• Start (date/time),

• Prescribed duration (only in assessment time 0),

• Delivered duration (only at assessment time 24 or last assessment time before treatment interruption/end),

• Prescribed blood flow rate (only at assessment time 0),

• Dialysate (ml/24 hours),

• Effluent (ml/24 hours; only at assessment time 24 or last assessment time before treatment interruption/end),

• Total volume removed from patient (ml/24 hours; only at assessment time 24 or last assessment time before treatment interruption/end),

• Type of haemodialyzer (as above),

• Surface (m^2^),

• Type of buffer,

• Anticoagulation (as above),

• Arterial site of vascular access (as above),

• Venous site of vascular access (as above),

• Type of vascular access (as above),

• Vascular access gauge,

• Treatment interrupted (date/time),

• Resumption of treatment (specify date/time),

• End (day/time),

• Change in modality.

The CRF for **CVVHDF **will require data entry at 0 hours, at 1 hour, 3 hours, 6 hours, 12 hours, 24 hours, and every 24 hours thereafter and at treatment end. Assessment times at 1.0, 3.0, 6.0 and 12.0 are optional, while assessment times at 24.0 and for multiples of 24 are mandatory. The CRF will automatically indicate the different assessment times (i.e. 0.0, 1.0, 3.0, 6.0, 12.0, 24.0, and so forth). The following information will be requested:

• Decision taken (date/time),

• Start (date/time),

• Prescribed duration (hours; only at assessment time 0),

• Delivered duration (hours; only at assessment time 24 or last assessment time before treatment interruption/end),

• Prescribed blood flow rate (ml/min; only at assessment time 0),

• Prescribed effluent (ml/hour; only at assessment time 0),

• Delivered effluent (ml/ 24 hour; only at assessment time 24 or last assessment time before treatment interruption/end),

• Prescribed reposition rate (ml/hour),

• Delivered reposition rate (ml/24 hours; (only at assessment time 24 or last assessment time before treatment interruption/end),

• Dialysate (ml/24 hours; only at assessment time 24 or last assessment time before treatment interruption/end),

• Total volume removed from the patient (ml/24 hours; only at assessment time 24 or last assessment time before treatment interruption/end),

• Type of haemodialyzer (as above),

• Surface (m^2^),

• Type of buffer,

• Anticoagulation (as above),

• Arterial site of vascular access (as above),

• Venous site of vascular access (as above),

• Type of vascular access (as above),

• Vascular access gauge,

• Treatment interrupted (date/time),

• Resumption of treatment (specify date/time),

• End (day/time),

• Change of modality.

Independently of modality chosen, all 'Modality-specific assessment time' CRFs include the following additional fields:

• SOFA (full set of data; only at assemement time 24 and for multiples of 24),

• Creatinine,

• Urea,

• Na,

• K,

• White blood cells (10^3^/μl),

• Platelets (10^3^/μl),

• Hb,

• pH,

• PaO_2_,

• PCO_2_,

• Bicarbonate,

• FiO_2_,

• Body temperature,

• Urine volume,

• Fluid balance (only at assessment time 24),

• Bicarbonate,

• Fractional inspired oxygen,

• Urine volume (ml/24 hours),

• Fluid balance (ml/24 hours),

• Systolic blood pressure (mmHg),

• Diastolic pressure (mmHg),

• Mixed venous oxygen saturation,

• Heart rate,

• Cardiac output,

• Cardiac index

• Pulmonary artery pressure,

• Systemic vascular resistance index,

• Intravascular blood volume index,

• Extravascular lung water index,

• Stroke volume variation,

• Vasopressor administration (milligrams of vasopressors/previous 24 hours): adrenaline (μg/kg per min), noradrenaline (μg/kg per min), dobutamine (μg/kg per min), dopamine (μg/kg per min), vasopressin (units/previous 24 hours), terlipressin (mg/previous 24 hours),

• Vasodilator administration,

• Other treatments: steroids (mg/24 hours; specify what type), recombinant human activated protein C, antithrombin III, protein C,

• Coagulation: activated partial thromboplastin time (diff versus control), activated clotting time (diff versus control), INR (%),

• Factors complicating RRT: logistics, organization, vascular access, anticoagulation, circuit patency, haemodialyzer performance.

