Despite the numerous publications that suggest a benefit from delivering higher dialysis doses (for review [25]), the real impact in critically ill patients is unclear. An observational clinical survey to evaluate what modality, for what reasons and what outcomes are important is needed if we are to understand how dialysis is delivered and at what dose in routine ICU practice; what the benefits, if any, are in terms of haemodynamics; and, finally, what are the benefits in terms of patient outcome as the primary end-point.

Current treatments for multiorgan dysfunction with ARF include many forms of CRRT that differ with respect to following factors: dose of dialysis, the extent of convection and diffusion, flow rates (blood, dialysate and replacement fluids) and anticoagulation protocols (heparin, citrate, flushes of saline). Ancillary to these factors are the choices of predilution or postdilution, of haemodialyser (surface, membrane) and of vascular access. It is still unknown whether and to what extent the prescribed dose comforms with evidence-based literature and, more importantly, how the delivered dose diverges from the prescribed one.

The present study, as indicated in the present protocol, should help to resolve at least some aspects of this still largely undefined area of critical care.

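### Prescribed effluent is recorded once (CVVH, CVVHDF) or not at all (CVVHD), so after the first 24 hours the gap between delivered and prescribed dose cannot be separated from changes in prescription

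*Protocol article*

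**What the plan says.** The field lists are in the protocol article, section Case report form: Modality-specific assessment time (step 3).

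- **CVVH.** Two prescribed volumes are listed, each tied to the start: "Prescribed effluent (ml/hour; only at assessment time 0" and "Prescribed reposition rate (ml/hours; only at assessment time 0". The delivered counterpart is "Total effluent (ml/24 hours; only at assessment time 24 or last assessment time before treatment interruption/end".
- **CVVHDF.** Prescribed effluent carries the same time-0 limit. Prescribed replacement fluid appears as "Prescribed reposition rate (ml/hour", with no time limit.
- **CVVHD.** The only prescribed items are duration and "Prescribed blood flow rate (only at assessment time 0". Dialysate appears as "Dialysate (ml/24 hours", not labelled as prescribed, and effluent as a 24-hour volume.

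For the continuous modalities the visit schedule says that "assessment time at 24.0 and for multiples of 24 are mandatory".

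Under Guidelines given in the CRF, a change of modality requires a new form, and a treatment begun after a treatment end counts as new. A change of dose within a modality is not mentioned.

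The Discussion says it is still unknown how far prescription follows the evidence and, "more importantly, how the delivered dose diverges from the prescribed one".

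**The concern.** Comparing delivered with prescribed dose needs the prescription that applied while the volume was delivered. These forms fix the prescription at the start of a treatment that may run for days. If the order is changed under way and the modality stays the same, later volumes are divided by the wrong denominator. A lowered order then looks like under-delivery, and a raised order masks it.

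At stake is a descriptive aim to which the article gives weight. The Introduction also reports prescribed against delivered ultrafiltration rate as a result of the group's preliminary study. A prescription that was not entered may be hard to recover later, because data are anonymous and a closed form can be corrected only on written request.

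**Working it through.** The plan states no figure on this point, so there is none to reproduce. The check compares the forms and then illustrates the size of the error.

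**Step 1: the forms side by side**

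| Form | Prescribed volume | Delivered volume (per 24 h) |
|---|---|---|
| CVVH | effluent and reposition, time 0 only | effluent and reposition, at 24 h or last assessment |
| CVVHD | none | dialysate, no time given; effluent, at 24 h or last assessment |
| CVVHDF | effluent, time 0 only; reposition, no time limit | effluent, reposition and dialysate, at 24 h or last assessment |

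The open-ended CVVHDF reposition entry covers only the replacement-fluid part of the effluent. No prescribed dialysate is listed, so an updated prescribed effluent cannot be rebuilt from it.

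**Step 2: both readings of the delivered field**

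- If delivered volume is entered at every multiple of 24 h, each day after the first is set against the time-0 prescription.
- If it is entered only at 24 h and at the last assessment, the last value is the one furthest from time 0.

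The mismatch after 24 h is present on either reading.

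**Step 3: one day's ratio**

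Inputs: 80 kg is the median Australian weight quoted in the Introduction. 25 ml/kg per hour is the dose derived there from 2 l/hour at that weight. 35 ml/kg per hour is the upper limit of CVVH in postdilution under Criteria to initiate RRT. Both rates are therefore CVVH, and no new form opens. The changes and the down-time are assumptions.

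Recorded ratio = (rate in force × 24 × fraction delivered) / (time-0 rate × 24)

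- Time-0 rates: 35 × 80 = 2800 ml/h; 25 × 80 = 2000 ml/h.
- Lowered from 2800 to 2000, fully delivered: 48,000 / 67,200 = 0.714. The true ratio is 1.00.
- Raised from 2000 to 2800, 20% down-time: 2800 × 24 × 0.8 = 53,760, and 53,760 / 48,000 = 1.12. The true ratio is 0.80.

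**Step 4: a whole course**

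Let r be the true delivered/prescribed ratio, c the proportional change in prescription at 24 h, and T the course length in hours. All three are assumed.

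Apparent ratio = r × [24 + (1 + c)(T − 24)] / T

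With r = 0.90:

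| Change c | T = 24 | T = 48 | T = 72 | T = 120 |
|---|---|---|---|---|
| −30% | 0.90 | 0.765 | 0.72 | 0.684 |
| −20% | 0.90 | 0.81 | 0.78 | 0.756 |
| none | 0.90 | 0.90 | 0.90 | 0.90 |
| +20% | 0.90 | 0.99 | 1.02 | 1.044 |

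Example: 0.90 × (24 + 0.8 × 48) / 72 = 0.90 × 62.4 / 72 = 0.78.

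With no change there is no error. If the prescription is recorded for each interval, the ratio returns to 0.90 whatever the change.

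**The case against.** The case against has several parts, and most of them narrow the point.

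- **No end-point uses the ratio.** The end-points are delivered dose with its outcome measures, and haemodynamic response. The questions listed in the Conclusion ask for delivered dose and reasons for down-time, not for divergence from prescription. This stands. A reader might infer that a stated study question will be answered wrongly, but the article defines no such ratio and fixes no analysis of it.
- **Down-time is recorded directly.** Interruption and resumption times, prescribed and delivered duration, and factors complicating RRT are all on the forms. This stands, so it would be wrong to say that down-time or its causes are hidden. These fields do not supply the prescription in force, however. Volume divided by running hours gives the achieved rate, and in the first example 2000 ml/h would fit either a lowered order or an unmet one.
- **Daily entry of delivered volume is an inference.** The field text names 24 h or the last assessment, whereas the SOFA field explicitly names multiples of 24. This stands, but Step 2 shows that the conclusion does not depend on it.
- **Some changes are captured.** CVVHDF reposition has no time limit. Raising postdilution CVVH above 35 ml/kg per hour makes it high volume haemofiltration, a different modality with a new form. Treatment end also covers changed clinical or other factors, which might restart time 0. So it cannot be said that no change is ever recorded. Whether adjusting the rate on a running circuit counts as treatment end is unclear, because the guidance speaks of another RRT being started.
- **The article is condensed.** The electronic forms are not shown, and a CVVHD prescribed field may exist there. That is possible. But the lists are itemised, the other two forms name the field, and the time-0 limit is a stated rule rather than an omission.

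**Conclusion.** The point holds in a limited form. On CVVH and CVVHDF, divergence of delivered from prescribed effluent after the first 24 hours cannot be told apart from a changed prescription. On CVVHD, as listed, it cannot be formed. The primary delivered-dose analysis uses no prescribed field and is untouched.

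It would go too far to conclude that a changed prescription is always read as failed delivery. The direction depends on the change: 71% recorded against a true 100% in one example, 112% against a true 80% in the other. These sizes rest on assumed changes. The article gives no frequency of within-modality changes, so the average bias is unknown, and it is zero where prescriptions stay constant. The first 24 hours are sound only if the order did not change within them.

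**What to change.** 1. On the CVVH, CVVHD and CVVHDF forms, record prescribed effluent, and prescribed dialysate where used, at time 0 and at every mandatory 24-hour assessment, with the date and time of any change.
2. State in the delivered-volume fields that they are entered at 24 h and at multiples of 24 h, as is done for SOFA, as well as at the last assessment.
3. Compute delivered/prescribed for each interval against the prescription in force.

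If the forms cannot be changed, limit the comparison to the first 24 hours and to modalities with a prescribed field, and say so when reporting. Pulse high volume haemofiltration should then be kept apart, since by its own definition the rate changes within the day.

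The cost is one or two extra entries at visits that already exist. Nothing about treatment changes, so the study stays observational.

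### On the continuous-RRT forms, delivered volumes are requested at hour 24 and at the last assessment before a stop, so read literally part of every uninterrupted run beyond about 48 h has no delivered dose recorded

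*Protocol article*

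**What the plan says.** All places are in the protocol article, mainly under 'Case report form: Modality-specific assessment time (step 3)'.

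- **Schedule.** The CVVH, CVVHD and CVVHDF forms are due at 0, 1, 3, 6, 12 and 24 h, every 24 h after that, and at treatment end. For CVVH: "Assessment times at 1.0, 3.0, 6.0 and 12.0 are optional, while assessment time at 24.0 and for multiples of 24 are mandatory". The other two forms carry the same rule.
- **CVVH volumes.** "Total effluent (ml/24 hours; only at assessment time 24 or last assessment time before treatment interruption/end" and "Total reposition (ml/24 hours; only at assessment time 24 or last assessment time before treatment interruption/end".
- **CVVHDF volumes.** "Delivered effluent (ml/ 24 hour; only at assessment time 24 or last assessment time before treatment interruption/end". Reposition, dialysate, volume removed and delivered duration carry the same limit.
- **CVVHD.** "Effluent (ml/24 hours; only at assessment time 24 or last assessment time before treatment interruption/end". Delivered duration and volume removed are limited likewise.
- **Fields without a limit.** On CVVHD, "Dialysate (ml/24 hours" stands with no timing clause. On CVVH, "Total volume removed from the patient (ml/24 hours" also has none, nor do delivered duration and delivered blood flow.
- **A field that is meant to be daily.** "SOFA (full set of data; only at assemement time 24 and for multiples of 24".

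The Abstract names delivered dose as the primary end-point, to be compared with mortality and other outcomes. 'Calculation of dialysis dose' equates CVVH clearance with the ultrafiltration rate (in postdilution). It derives CVVHD clearance from delivered operating parameters, through a blood flow versus clearance relationship for each haemodialyser.

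**The concern.** The forms distinguish two timings. SOFA is tied to hour 24 and its multiples. The delivered volumes are tied to hour 24 alone, or to the last assessment before a stop, and the clause begins with 'only'. An electronic form programmed to that wording would not open the effluent field at 48 h, 72 h or later unless that visit turned out to be the last. The visit takes place, but the number that the study is about is not requested.

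The Discussion says it is unknown how delivered dose diverges from prescribed dose, and the Conclusion makes the effect of delivered dose on outcome the ultimate goal. With volumes only from the first day and one later day, a long treatment course is represented by a sample of its days. Day-to-day variation then acts as measurement error in the exposure and would bias a dose-mortality slope towards zero. Late repair is awkward, because 'Materials and methods' allows no change to a closed form without a written request.

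There is also a unit problem. A last entry that covers fewer than 24 h is still labelled ml/24 hours. One centre could enter the volume measured and another a 24 h extrapolation, and the recorded value would not show which.

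**Working it through.** The protocol states no coverage figure, so there is none to reproduce. The check has two parts.

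**1. Share of a run with a recorded volume**

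Inputs: the timing clause above, and a 24 h look-back per entry, taken from the unit ml/24 hours. Run length T is assumed, because the protocol gives none. The run is uninterrupted.

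For T above 48 h there are two entries of 24 h each, one at hour 24 and one at the last assessment:

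coverage = (24 + 24) / T = 48 / T

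| T (h) | 48/T | Daily entries, none at end | Daily entries plus end |
|---|---|---|---|
| 60 | 80% | 80% | 100% |
| 72 | 67% | 67% | 100% |
| 84 | 57% | 86% | 100% |
| 96 | 50% | 75% | 100% |
| 120 | 40% | 80% | 100% |
| 168 | 29% | 86% | 100% |
| 240 | 20% | 90% | 100% |

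The 48/T column is the same whether or not the treatment-end form counts as the last assessment. Only the position of the gap changes. At 72 h, if the end form counts, hours 0-24 and 48-72 are covered and the middle day is missing. If it does not, hours 0-48 are covered and the last 24 h are missing. At 120 h, three of five days are missing either way.

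For runs up to 48 h the two readings diverge. A 48 h run is 100% covered if the end form counts and 24/48 = 50% if it does not.

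**2. Effect on the slope, if the exposure is the course average**

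Inputs from 'Statistical analysis, Primary end-point': clearance mean 29.8, SD 10.0, event rate 0.51 at the mean, log odds ratio -0.22 per unit, n = 110, two-sided alpha 0.01. The plan's own figures reproduce: ln[(0.25/0.75)/(0.51/0.49)] / (35.0 - 29.8) = -0.219, and the odds ratio over 5.2 units is 0.32.

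Assumptions not in the protocol: 5-day runs, independent day-to-day deviations with SD 5, 8 or 10, and mortality driven by the course-average dose.

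Simulated logistic regression, median fitted slope (odds ratio over 5.2 units = exp(5.2 × slope)):

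| Day-to-day SD | First plus last day | All five days |
|---|---|---|
| 5 | -0.190 (OR 0.37) | -0.215 |
| 8 | -0.165 (OR 0.42) | -0.228 |
| 10 | -0.145 (OR 0.47) | -0.232 |

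First plus last day is the case that matches the forms. With all days recorded, the slope stays at about -0.22. In the same setting, power at alpha 0.01 remains about 100% with first-plus-last capture, so the estimate is distorted but the test of no relationship is not endangered.

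**3. Which doses depend on the limited fields**

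- CVVH: dose is the ultrafiltration rate, which needs effluent, or reposition plus volume removed. The unrestricted fields (volume removed, duration, blood flow) do not give it on their own.
- CVVHDF: effluent, reposition, dialysate and delivered duration are all limited.
- CVVHD: dialysate is not limited, and dose is built from operating parameters, not from effluent.

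**The case against.** The best defence is that hour 24 is shorthand for each 24 h assessment. The schedule is daily and mandatory, the unit is ml/24 hours, and the field list is loosely worded elsewhere: fluid balance appears once limited to hour 24 and once as an unrestricted 24 h field. The article summarises an electronic form that is not shown. On that reading no complete day is lost. This may be what was meant, and it weakens the SOFA contrast as evidence of intent. It does not remove the defect: the printed rule says something else, and a programmer or a centre following it would skip the later days.

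Three stronger readings are tempting, and the document does not support them.

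- **That most treatment days are lost.** Coverage falls below half only in uninterrupted runs longer than 4 days (48/96 = 50%). No run lengths are given, and each interruption triggers a further entry.
- **That the final hours of every run are lost.** Data entry is also required at treatment end, and end, interruption and resumption times are recorded. The clause can be read as the closing entry of the run. The point is ambiguous.
- **That dose is represented by day 1 alone, or that the missing days never enter the exposure.** The forms give the first day plus the last assessment, so the larger attenuation from a day-1 exposure is not the relevant figure. The protocol does not say whether the exposure is the first 24 h, a daily mean or the whole course. If it were the first 24 h, the missing later days would not matter to it.

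**Conclusion.** The point holds for CVVH and CVVHDF, and in part for CVVHD. As printed, the timing clause leaves delivered effluent and related volumes unrequested at mandatory visits after hour 24 unless that visit is the last before a stop. An uninterrupted run longer than about 48 h then has 48/T of its hours recorded: 67% at 72 h, 50% at 96 h, 40% at 120 h. These percentages rest on the literal wording, a 24 h look-back and assumed run lengths.

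The consequence for the slope, from -0.22 to roughly -0.19 to -0.15, is conditional on a course-average exposure, 5-day runs and a day-to-day SD of 5 to 10, none of which the protocol states. The description of delivered dose in current practice is also affected, because later treatment days would be under-represented.

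Capture of the final hours and the meaning of a sub-24 h entry in ml/24 hours are open questions in the text, not demonstrated losses. Since the rule bears on the study's primary quantity and is cheap to correct, it should be corrected before recruitment starts, even if daily capture was intended all along.

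**What to change.** On the CVVH, CVVHD and CVVHDF forms:

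1. Request effluent, reposition, dialysate (each where the form has it) and delivered duration at 24 h, at every multiple of 24 h, at each interruption and at treatment end.
2. Replace the ml/24 hours unit for these fields with two numbers: volume since the previous entry (ml) and hours covered.
3. For doses taken from volumes, compute delivered dose as the sum of the recorded volumes divided by the sum of the hours covered, and state whether the patient-level exposure is this course average or another summary.

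With this change, coverage is 100% for any run length, and the ambiguities about the final hours and partial days disappear. The cost is a change of wording and programming in the electronic form, plus a few more numbers per entry. The 24 h visits are already mandatory and entry at treatment end is already required.
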